## Abstract

**Background:**

Cellular therapies have been increasingly applied to diverse human diseases. Intracoronary infusion of bone marrow-derived mononuclear cells (BMMNC) has demonstrated to improve ventricular function after acute myocardial infarction. However, less information is available about the role of BMMNC therapy for the treatment of dilated myocardiopathies (DCs) of non-ischemic origin. This article presents the methodological description of a study aimed at investigating the efficacy of intracoronary injection of autologous BMMNCs in the improvement of the ventricular function of patients with DC.

**Methods:**

This randomised, placebo-controlled, double-blinded phase IIb clinical trial compares the improvement on ventricular function (measured by the changes on the ejection fraction) of patients receiving the conventional treatment for DC in combination with a single dose of an intracoronary infusion of BMMNCs, with the functional recovery of patients receiving placebo plus conventional treatment. Patients assigned to both treatment groups are monitored for 24 months. This clinical trial is powered enough to detect a change in Left Ventricular Ejection Fraction (LVEF) equal to or greater than 9%, although an interim analysis is planned to re-calculate sample size.

**Discussion:**

The study protocol was approved by the Andalusian Coordinating Ethics Committee for Biomedical Research (*Comité Coordinador de Ética en Investigación Biomédica de Andalucia*), the Spanish Medicines and Medical Devices Agency (*Agencia Española de Medicamentos y Productos Sanitarios*), and is registered at the EU Clinical Trials Register (EudraCT: 2013–002015-98). The publication of the trial results in scientific journals will be performed in accordance with the applicable regulations and guidelines to clinical trials.

**Trial registration:**

ClinicalTrials.gov Identifier NCT02033278 (First Posted January 10, 2014): https://clinicaltrials.gov/ct2/show/NCT02033278; EudraCT number: 2013–002015-98, EU CT Register: https://www.clinicaltrialsregister.eu/ctr-search/search?query=2013-002015-98. Trial results will also be published according to the CONSORT statement at conferences and reported peer-reviewed journals.

## Background

### Background and rationale

In the last few years we have assisted to a large increase on the use of cellular therapies, propelled by the identification of stem cells with regenerative properties in virtually all adult tissues. This has been particularly notorious in the field of cardiology, probably due to the high prevalence of cardiac diseases and the easy monitorization of cardiac function.

Recent research in the field has changed the concept of the heart as an organ exclusively constituted by postmitotic cells and, therefore, unable to regenerate. According to this dogma maintained for decades, the number of cardiac myocytes each individual is born with, is maintained throughout their life and if some myocytes dies (for example, as a result of a heart attack) they cannot be replaced in any way. Initial observations by Anversa et al. [1] seriously questioned this concept by demonstrating the capacity for myocardial regeneration from resident cells after acute myocardial infarction (AMI). Nowadays, several randomized studies and meta-analyses demonstrate a significant improvement in post-AMI ventricular function following intracoronary infusion of autologous bone marrow-derived mononuclear cells (BMMNC) [2–10]. Even though the role of cellular therapy in the treatment of ischemic heart disease has been extensively studied [11], its potential application to other causes of congestive heart failure that still constitute an important cause of cardiovascular mortality has not been explored in depth. Such is the case of dilated myocardiopathies (DCs) of non-ischemic origin, which constitute a major cause of heart failure. This group of primary myocardial diseases is characterized by a loss of cardiomyocytes along with an increase of fibroblasts in cardiac tissue. Therefore, restoring cardiomyocytes using autologous bone marrow (BM) cells could constitute an effective therapy for DC, improving cardiac function.

Different experimental studies in animal models of DC have shown improvements in ejection fraction and decreases in the ventricular volumes after cell therapy [12–21]. These benefits have also been established in clinical studies aimed at analysing the safety and efficacy of bone marrow-derived progenitor cells in patients with DC [22–31]. In 2006, the ABCD trial [26] described for the first time in humans improvements in the NYHA functional class, a decrease in end-diastolic volume and an average improvement of 5.4% in the ejection fraction in 24 patients with DC treated with intracoronary BM-derived cells. A long term follow-up of this trial showed that the functional benefits achieved were maintained without late adverse effects [25]. Similarly, Fischer-Rasokat et al. [23] observed in 33 patients with DC that intracoronary administration of BM-derived cells appears to be associated with improvements in cardiac contractile and microvascular function in patients with DC (ref). More recently, these results have been confirmed by the REGENERATE-DCM clinical trial [30], in which a 5.37% increase in left ventricular ejection fraction (LVEF) was observed at 3 months after treatment with autologous BM-derived cells combined with peripheral granulocyte colony-stimulating factor (G-CSF). Next to these previous experiences, our group has completed a one-year Phase II Clinical Trial (NCT00629096, EudraCT 2007–003088-36) to evaluate the safety and efficacy of intracoronary infusion of autologous BMMNCs in 27 patients with DC [32]. In this study, an improvement in the New York Heart Association (NYHA) functional class and a reduction of brain natriuretic peptide (BNP) plasma levels were observed without any adverse effect. In addition, a significant decrease in ventricular volumes along with a mean increase in the ejection fraction of 9% in 20 out of the 27 patients was observed at month 6. These changes suggest a favourable effect of cell therapy on ventricular remodelling, which may explain the decrease (or even disappearance) of the degree of mitral regurgitation observed in some patients. However, the gain in ejection fraction after cell therapy varied greatly between patients, ranging from − 9% to + 34%, being this gain greater in patients with a baseline ejection fraction < 25%. The clinical benefit of cell therapy was stable 5 years after infusion, with 69% survival rate and 43% of patients free of major events, staying within a NYHA functional class of I-II [33]. Interestingly, younger patients seemed to show the highest long term response to cell-based therapy in terms of LVEF improvement. However, contradictory reports have been published which show no improvements in ejection fraction, NYHA functional class, or exercise test outcomes after intracoronary infusion of autologous BMMNCs in patients with DC [29]. However these findings should be interpreted with caution as, despite apparent similarities, important methodological differences exist among published reports: BMMNCs dose, LVEF measuring technique, administration procedure, clinical description of eligible patients, subject follow-up length, use of G-CSF, technique of bone marrow cell harvesting etc. Ultimately, clinical studies using BM-derived cells in DC patients have shown only modest benefits [34–36]. We believe that the proposed clinical study may contribute with a new methodological perspective on search for cell therapy-based treatment alternatives in patients with DC. In summary, there is sufficient preliminary evidence to consider intracoronary injection of BMMNCs as a viable, safe and beneficial treatment in patients with DC. However, there is a need for larger, randomized, controlled studies to understand the biological mechanism of action of BMMNCs in the myocardium and the factors affecting clinical response to regenerative therapy with autologous BMMNCs in patients with DC.

### Objectives

This article presents and discusses the methodological description of a randomized, placebo-controlled, double-blinded phase IIb clinical trial aimed at evaluating the efficacy of intracoronary injection of autologous BMMNCs in improving ventricular function among patients with idiopathic DC, for which there is currently no effective therapeutic alternative. The secondary objectives of the study are: to analyse the clinical, functional and biological factors that predict a good response to the BMMNC therapy; as well as to confirm the safety of the product and the route of administration.

## Methods and design

### Trial design

The study is designed as randomized, placebo-controlled, double-blind phase IIb clinical trial to compare the functional recovery of patients receiving the conventional treatment for DC in combination with an intracoronary infusion of BMMNCs, using placebo as a control. A 2:1 BMMNC/placebo allocation ratio is used for the randomization of a total of 51 eligible patients. Therefore, a total of 34 subjects will receive BMMNCs infusion, whereas 17 subjects will be treated with a placebo infusion. In order to analyse the predictors of clinical response as well as safety variables, all trial subjects (*n* = 51) are followed for a period of 24 months, completing a total of nine study visits: screening (visit 1), randomization (visit 2), infusion (visit 3), 24 post-infusion (visit 3.1), and months 3 (visit 4), 6 (visit 5), 12 (visit 6), 18 (visit 7) and 24 (visit 8) after the BMMNC/placebo administration (Fig. 1). To allow for sample size re-calculation an interim analysis will be performed with the data from the 6 months post-infusion period of the first 20 patients included. A second interim analysis is planned when the last patient included in the trial has completed study visit 5 (6 months). This early analysis of the data may provide conclusive efficacy (and safety) evidence in order to allow for the authorization of compassionate treatment of finalized patients allocated to placebo. On-completion of protocol standardized 24 months’ follow-up, all patients receiving the experimental treatment will be followed on an observational scheme for an additional period of up to 5 years. This extended follow-up period will provide long term efficacy and safety data of BMMNCs infusion.

**Fig. 1 Fig1:**
[figure not shown]
Study design and assessment timeline. Clinical trial visits are structured in 9 time-points, that include two pre-infusion visits (screening and randomization), BMMNC/placebo infusion day, and 6 post-infusion follow-up evaluation time-points according to a decreasing frequency: 24 h, 3 months, 6 months, 12 months, 18 months and 24 months. The procedures and evaluations performed are detailed for each visit. Biochemical determinations: glucose, urea, creatinine, sodium, potassium, C reactive protein (CRP), aspartate aminotransferase (AST), alanine aminotransferase (ALT), gamma-glutamyl transferase (GGT), alkaline phosphatase (ALP), bilirubin, total cholesterol, HDL-cholesterol, LDL-cholesterol, triglycerides, lactate dehydrogenase (LDH). Cardiac enzymes: Creatine kinase (CK), Troponin I or US and brain natriuretic peptide (BNP) or N-terminal fragment of pro-brain natriuretic peptide (NT-proBNP). Demographic data: date of born, sex. Echocardiogram (Echo): Left ventricular (LV) ejection fraction (LVEF, %), LV end-diastolic volume (LVEDV, ml), LV end-systolic volume (LVESV, ml), LV end-diastolic diameter (LVED, mm), LV end-systolic diameter (LVSD, mm), left atrial (LA) area (cm2), right ventricular (RV) end-diastolic volume (RVEDV, ml), Tricuspid annular plane systolic excursion (TAPSE, mm). Electrocardiogram (ECG): synusal rhythm, conduction disturbances, atrial fibrillation (AF), right bundle branch block (RBBB), left bundle branch block (LBBB), left anterior hemiblock (LAHB), QRS duration (sec), PR duration (sec), heart rate (bpm). Exercise testing (ExTest) (according to Naughton protocol): Metabolic equivalents (METS), exercise time (min). Hemogram: red blood cell (RBC) count, hemoglobin, hematocrit, white blood cell (WBC) count (neutrophils, lymphocytes, monocytes, eosinophils, and basophils), erythrocyte sedimentation rate (ESR), platelets. Medical history: personal antecedents, cardiovascular risk factors (hypertension, dyslipidemia, tobacco and alcohol consumption, history of ischemic cardiomyopathy). Clinical evaluation: adverse events (AEs), concomitant drugs and procedures evaluation. Serology: human immunodeficiency virus (HIV), Hepatitis B virus (HBV), Hepatitis C virus (HCV). Tumoral markers: CA125, CA19.9, carcinoembryonic antigen (CEA), and alpha-fetoprotein (AFP), Beta-hCG (BHCG), prostate-specific antigen (PSA). Ventriculography: LVEF in sinus rhythm (%), LVEF in sinus rhythm post-PVC (premature ventricular contraction) (%), Sinus end-diastolic volume (mL/m2), Sinus end-systolic volume (mL/m2), Post-PVC end-diastolic volume (mL/m2), Post-PVC end-systolic volume (mL/m2), hypokinesia in sinus rhythm, hypokinesia post-PVC, acute coronary syndrome (ACS) in sinus rhythm, ACS post-PVC, left ventricular end-diastolic pressure and heart rate (bpm). Vital signs: blood pressure (mmHg), heart rate (bpm)

This is an investigator-driven clinical trial lead by an team of cardiologist and hematologist, and sponsored by the Andalusian Initiative for Advanced Therapies (AIAT), through the Andalusian Public Foundation Progress and Health, acting as a coordinating and advisory entity to help with the complex regulatory requirements needed for clinical implementation of basic research findings [37]. AIAT is also responsible for handling clinical trial administrative authorizations and regulatory affairs, providing study drug and supplies, independent data and safety monitoring, centralised manufacturing supervision, as well as general coordination and daily operational management of the trial for all of the participating sites. Patients or public where not involved in the design, conduct or recruitment of the trial, yet trial results will be disseminated to the public through the EU Database, as well as patient’s congresses wherever possible.

### Study outcomes

The main study variable is the improvement on the ventricular function measured angiographicaly as described below. This efficacy outcome is measured as the changes on the LVEF evaluated by a cardiologist blinded to the patients’ clinical follow-up. With this objective, patients undergo cardiac catheterization in two study timepoints: on the date of the intracoronary infusion of either experimental treatment or placebo (visit 3) and at month 6 (visit 5) after infusion.

Secondary efficacy outcomes include clinical evaluation and NYHA functional grade, BNP or N-terminal fragment of pro-brain natriuretic peptide (NT-proBNP) blood levels, echocardiogram, exercise testing according to Naughton protocol, without oxygen consumption as well as biological parameters of the BMMNC product that may predict a good response (cellularity, chemotaxis and stem cell markers: CD133+, CD34+, CD34+/CD177+,CD34+/CD38-, CD34+/CXCR4+, CD34+/DR-, VEGFR2+, CD90+, CD105+, CD73+, CD14-, CD45-).

Study variables regarding safety are measured as appropriate during follow-up visits: adverse events (AEs) and serious adverse events (SAEs), causally related with study interventions or procedures (including marked changes of vital signs, abnormalities physical examinations and out of range laboratory test results). Additionally, the protocol emphasizes the identification of specific adverse events: major cardiac events or MACEs (defined as cardiac death, major arrhythmia, inclusion in heart transplant waiting list, cardiac resynchronization therapy interventions and hospital admission due to clinically relevant adverse cardiac events), symptoms and signs of arrhythmia, evidence of myocardial harm and tumoral biomarkers abnormalities.

The study design, evaluations and assessment timeline for all variables is illustrated in Fig. 1. After product infusion, all patients are followed-up for 24 months according to protocol by interventional or clinical cardiologists at the participating hospitals. Protocol programmed visits are structured in 9 time-points that include two pre-infusion visits (screening and randomization), BMMNC/placebo infusion day, and 6 post-infusion follow-up evaluation time-points according to a decreasing frequency: 24 h, 3 months, 6 months, 12 months, 18 months and 24 months. Trial investigators must ensure that essential clinical, analytical and exploratory data is registered in the study’s Case Report Form (CRF).

### Study population and enrolment

The study population is constituted by adult male and female patients diagnosed with idiopathic DC, meeting all eligibility criteria as described in Table 1. A sample size of 51 subjects who are regularly followed-up in the Cardiology Units of the eight participating University Hospitals from the Andalusian Public Health System (Table 2) are included in the study through a competitive recruitment scheme. Before undergoing any trial-related procedures, all patients willing to participate in the study must sign a written informed consent. Study practitioners provide them with information about the study, the investigational product, the purpose, procedures and potential risks and benefits of the study. They are randomly assigned to the experimental or control group following a 2:1 ratio, and are engaged to complete study follow-up visits through an optimised medical attention. Trial subjects can withdraw consent for trial participation at any time. Once the patient has received treatment, withdrawal of consent is the single exclusion criteria considered by the protocol. In all other cases the patient must complete follow-up visits to meet at least safety objectives. In addition, patients who have not received the investigational product infusion can also leave the study when a SAE occurs, or the clinical situation of the patient changes and the investigator considers that an alternative treatment is needed.

**Table 1 Tab1:** Eligibility criteria

INCLUSION CRITERIA	
*Participants meeting all the following criteria will be included:*	
1. Male and female patients between 18 and 70 years old.	
2. Patients who sign the informed consent.	
3. Patient diagnosed with idiopathic dilated cardiomyopathy (using echocardiography).	
4. At least 6 months since dilated cardiomyopathy diagnosis.	
5. Lack of coronary injuries on multi-slice computerized axial tomography scan and/or hemodynamic study performed after the inclusion of the patient in the trial, or prior to recruitment if the patient does not present any angina symptomatology.	
6. Patients under optimised pharmacological treatment for at least 6 months prior inclusion in the trial.	
7. Left ventricular ejection fraction (LVEF) ≤ 40% or LVEF 40–50% if left ventricular end diastolic volume (LVEDV) > 110 ml/m^2^ (measured by echocardiogram).	
8. Presence of sinus rhythm.	
9. Normal levels of analytic indicators. Defined by: Leukocytes ≥3000c cel/mm^3^; Neutrophils ≥1500 cel/mm^3^; Platelets ≥100,000 cel/mm^3^; AST/ALT ≤2.5 institution standard range; Creatinine ≤2.5 mg/dl.	
10. Woman of childbearing age with a negative result on a pregnancy test performed at the time of the inclusion and committed to use contraceptive methods during the study.	
EXCLUSION CRITERIA	
*Participants meeting one or more of the following criteria will be excluded.*	
1. Secondary dilated cardiomyopathy	
2. Recent (6 months) myocarditis episodes prior to signing the informed consent.	
3. Patients susceptible to resynchronization therapy (QRS > 150, presenting symptoms and with no response to medication). However non-responders to resynchronization therapy within 6 months may be included.	
4. Patients in the waiting list for cardiac transplantation.	
5. Coexistence of any type of hematologic disorder, malignant or premalignant tumor, or other severe systemic diseases.	
6. Woman of childbearing age not using contraceptives, pregnant or in breastfeeding period.	
7. Patients currently taking part in another clinical trial or those who did so in the last 3 months or those who have participated in a clinical trial with advanced therapy at any time.	
8. Positive serology for hepatitis B, hepatitis C or human immunodeficiency virus.	
9. Patients taking medicines prohibited by protocol at the time of inclusion. A wash-out period of 2 months is established to be eligible for inclusion.

**Table 2 Tab2:** Study sites and enrolment distribution until December 2018

Clinical Trial Sites^a^	Enrolment
University Hospital Reina Sofía (Córdoba)	24
University Regional Hospital of Málaga	1
University Hospital Virgen del Rocío (Seville)	2
University Hospital Puerta del Mar (Cádiz)	0
University Hospital Virgen de las Nieves (Granada)	1
Hospital Costa del Sol (Marbella)	0
University Hospital Juan Ramón Jimenez (Huelva)	0
University Hospital of Jerez (Jerez de la Frontera)	0
University Hospital Virgen Macarena (Seville)	0
PARTICIPATING HOSPITALS = 9	28 SUBJECTS

^a^Participating hospitals may be subject to eventual changes as restrictive selection criteria and the low prevalence of this disease may demand flexible re-distribution of clinical trial sites in order to to complete the sample size

### Trial status

The first patient was included in February 2014, after the approval of the institutional Ethics Committees and the Spanish Medicines and Medical Devices Agency (*Agencia Española de Medicamentos y Productos Sanitarios, or AEMPS*), and is currently ongoing in nine Spanish hospitals (Table 2). At the time of manuscript submission patient recruitment is active with 27 patients having received the investigational medicinal product so far (53% of trial sample size, *n* = 51). The study will end when the trial’s sample size (*n* = 20) has been completed and the last patient recruited completes a 24 months’ follow-up period.

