### Sample size calculation

A sample size calculation was performed based on the clinical trial study already completed by our group [32]. In this study, a mean increase in ejection fraction of 9.4 ± 9.9% was observed. At the end of the follow-up, mean values of LVEF were 38% among responders, and 27% among non-responders. The sample size calculation was done using GRANMO (v7.12) for paired or repeated measures in two groups. Accepting an alpha risk of 0.05 and a beta risk of 0.2 in a two-sided contrast, 17 subjects are required in the first group and 34 in the second one to detect a difference equal to or greater than 9 units. It is assumed a common standard deviation of 10 and a correlation coefficient between the initial and final measurement of 0.5. A loss to follow-up rate of 10% has been estimated. However, an interim analysis has been planned in order to re-calculate trial sample size based on the mean increase in ejection fraction observed in the first 20 patients that complete a 6 months’ follow-up period.

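### The end-of-study rule under Trial status gives the trial's sample size as 20; the rest of the article gives 51

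*Protocol article*

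**What the plan says.** In the protocol article, Trial status contains two sample sizes in consecutive sentences. The first reports "27 patients having received the investigational medicinal product so far (53% of trial sample size, *n* = 51"), with recruitment still active. The second sets the end of the study at the point where the trial's "sample size (*n* = 20) has been completed and the last patient recruited completes" a 24-month follow-up.

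Three other sections state the trial size:

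- Trial design: "A 2:1 BMMNC/placebo allocation ratio is used for the randomization of a total of 51 eligible patients", and then "a total of 34 subjects will receive BMMNCs infusion, whereas 17 subjects will be treated with a placebo infusion".
- Study population and enrolment: "A sample size of 51 subjects who are regularly followed-up in the Cardiology Units".
- Sample size calculation: "17 subjects are required in the first group and 34 in the second one to detect a difference equal to or greater than 9 units".

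As a number of patients in this trial, 20 otherwise appears only for the first interim analysis, which re-calculates the sample size from the first 20 patients with 6 months of follow-up. It has that meaning in Trial design, Sample size calculation, Data management and statistical analysis, and the Discussion. No section lowers the target to 20.

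**The concern.** The sentence that says when the study ends should carry the same target as the powered design. Here it carries 20, less than half of 51, directly after a sentence that uses 51 as the denominator for recruitment progress. Both sentences refer to the trial's sample size, so they cannot both be right.

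The condition in the rule decides when recruitment counts as complete, and from that when the last 24-month visit falls. With 20 in the rule, the condition was already met when the article was submitted, and recruitment could be declared complete at any later number without breaching the text. The Discussion describes recruitment as difficult and the design plans two interim analyses, so the completion number should be unambiguous.

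**Working it through.** **1. Does 51 follow from the article's own inputs?** All inputs are in Sample size calculation, except the 2:1 allocation, which Trial design states outright: two-sided alpha 0.05, beta 0.2, difference 9 units, common SD 10, baseline–final correlation 0.5, loss to follow-up 10%.

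- SD of change = 10 × √(2 × (1 − 0.5)) = 10.
- Smaller arm, before losses: n = (1 + 1/2) × (10 × (1.960 + 0.842) / 9)² = 14.5, rounded up to 15. Larger arm: 2 × 15 = 30.
- Allowing for 10% loss: 15 / 0.9 = 16.7, rounded up to 17; 30 / 0.9 = 33.3, rounded up to 34.
- Total: 17 + 34 = **51**, an exact match.

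**2. Which figure fits the reported progress?**

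| Denominator | 27 infused | Stated |
|---|---|---|
| 51 | 27 / 51 = 52.9% | 53% |
| 20 | 27 / 20 = 135% | – |

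Table 2 shows 28 enrolled to December 2018 (24 + 1 + 2 + 1). Both 27 and 28 exceed 20, yet Trial status calls recruitment active.

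**3. What would the literal rule cost?** Twenty had already been passed, so the smallest trial a literal reading could still produce is the one in hand, 27 or 28 patients. The article does not report the split by arm. I assume about 2:1 and no losses, and use a two-sample t-test on the change in LVEF with SD 10 and a difference of 9 (power from the noncentral t distribution).

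| BMMNC : placebo | SE = 10 × √(1/n₁ + 1/n₂) | 9 / SE | Power |
|---|---|---|---|
| 18 : 9 | 4.08 | 2.20 | 56% |
| 19 : 9 | 4.05 | 2.22 | 57% |
| 30 : 15 (51 after 10% loss) | 3.16 | 2.85 | 79% |
| 34 : 17 (51, no loss) | 2.97 | 3.03 | 84% |

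The 79% at 30:15 is the planned 80% under the t distribution; the normal approximation gives 81%.

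**The case against.** The best reply is that the document answers the question itself. The preceding sentence gives 51, the 53% confirms it, recruitment continued beyond 20, and the footnote to Table 2 allows sites to be redistributed so that the sample size can be completed. On that view this is a slip in one parenthesis and not a second live target. That stands, and it is why the point is a simple correction and not a challenge to the design. It does not make the sentence right. An article may condense its protocol, but this is a figure stated wrongly and not a detail left out.

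A reader might go further than the text allows in four ways:

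- **A 20-patient trial with about 44% power.** That is the noncentral-t figure for 13:7, but with 27 already infused such a trial could no longer occur. The relevant worst case is the 27–28 patients above.
- **The 20 also fixes when the data are frozen or the main variable analysed.** Data management and statistical analysis ties the freeze to double entry, resolution of inconsistencies and quality control. It ties the second interim analysis to 6 months of follow-up in all recruited patients. Neither refers to 20.
- **The approved protocol carries the same error.** The article says it describes Amendment 7, but that document is not shown. Only the article's error is established.
- **The 20 is known to come from the first interim analysis.** That is the likely source, but it is an inference.

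**Conclusion.** The point holds as an internal inconsistency in a sample-size figure. The end-of-study rule says 20 where the adjacent sentence and three other sections say 51. It is not an arithmetic error: 51 reproduces exactly from the stated inputs, and 20 is not the result of any calculation in the article.

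Taken literally, the rule was already satisfied at 27 infused and 28 enrolled. Closing recruitment there would leave about 56–57% power for 9 points, against the planned 80%. Those figures assume 2:1 allocation, no losses and an SD of change of 10; losses would lower them. They show what a literal reading would cost and do not say that the trial stopped early. The inconsistency stands on the text alone. The context makes clear that 51 is intended, so a simple correction is enough.

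**What to change.** In Trial status, replace n = 20 in the end-of-study sentence with: n = 51, or the size set by the documented re-calculation. The second clause is needed because the first interim analysis may change the target. Keep 20 only where the first interim analysis is described. Check the full protocol for the same figure and correct it there if it appears.

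The cost is one line in the article and, if the full protocol is affected, the same line there through the usual amendment route. The design, the analysis and the planned recruitment do not change.
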